## **1.0 STUDY HYPOTHESIS AND OBJECTIVES:**

### **1.1 Hypothesis**

In HIV-positive subjects with central fat accumulation on ART, daily telmisartan therapy will be associated with a 10% reduction in visceral adipose tissue over 24 weeks.

### **1.2 Primary Objectives:**

1.2.1 To assess the median change in visceral adipose tissue (VAT) volume (measured by abdominal CT scan) over 24 weeks in HIV-positive subjects with central fat accumulation initiating telmisartan therapy.

1.2.2 To describe the safety and tolerability of telmisartan in HIV-positive men and women over the 24 week duration of the study.

### **1.3 Secondary Objectives:**

1.3.1 To assess changes in superficial adipose tissue (SAT) volume (by abdominal CT scan) over 24 weeks in HIV-positive subjects initiating telmisartan therapy.

1.3.2 To assess the change in VAT:SAT ration over 24 weeks in HIV-positive subjects initiating telmisartan therapy.

1.3.3 To assess the effects of telmisartan on serum lipid levels in HIV-positive subjects initiating telmisartan therapy.

1.3.4 To assess the effects of telmisartan on insulin sensitivity in HIV-positive subjects initiating telmisartan therapy.

1.3.5 To assess the effects of telmisartan on markers of inflammation in HIV-positive subjects initiating telmisartan therapy.

1.3.6 To compare Framingham risk scores at baseline and 24 weeks in HIV-positive subjects initiating telmisartan therapy.

1.3.7 To compare the prevalence of metabolic syndrome at baseline and 24 weeks in HIV-positive subjects initiating telmisartan therapy.

1.3.8 To measure changes in systolic and diastolic blood pressure in HIV-positive subjects initiating telmisartan therapy.

1.3.9 To assess changes in urinary protein excretion and serum creatinine in HIV-positive subjects initiating telmisartan therapy.

## 2.0 INTRODUCTION

### 2.1 Background and Rationale

In the context of HIV infection, the term lipodystrophy refers to a spectrum of changes in body fat redistribution and associated metabolic abnormalities, and is not precise. Fat abnormalities can be categorized as either lipoatrophy (fat loss) or lipohypertrophy (fat gain), with each syndrome having unique risk factors, clinical features, and treatments. Fat redistribution in HIV-infected subjects has been reported to range from 2%-84%, with the wide range reflecting a lack of consensus definition and diagnostic criteria.

Lipohypertrophy generally refers to fat accumulation in the abdomen, breasts, posterior neck (buffalo hump), and viscera. In the research setting, it is more specifically defined as a combination of patient-reported fat changes and an increased waist:hip ratio ( $>0.94$  in men and  $>0.88$  in women) or abdominal circumference ( $>95$  cm in men and  $>94$  cm in women). Cross-sectional imaging techniques such as computed tomography (CT) and magnetic resonance imaging (MRI) are the gold standard for measurement of body fat volume.

In observational and cross sectional studies, risk factors for lipohypertrophy have included protease inhibitor (PI) use, older age, white race, more advanced degree of immunosuppression, and female gender. However, recent prospective trials in treatment-naïve patients have called into question the role of PIs as a cause of lipohypertrophy. After 48 weeks of tenofovir + lamivudine with either ritonavir-boosted tipranavir- or lopinavir, both peripheral and visceral fat decreased in both groups. After 48 weeks of either a tipranavir- or ritonavir/lopinavir (LPV/TRV)-based regimen combined with emtricitabine, visceral fat decreased in both groups. It is unknown whether a longer course of treatment with a PI might have contributed to the development of lipohypertrophy. In ACTG 5142, an efavirenz-based regimen induced the same level of trunk fat increase as that seen in LPV/RTV arm^9, again questioning the role of PIs in inducing the abdominal fat accumulation seen in HIV-infected subjects.

Lipohypertrophy is a common and distressing problem for people living with HIV infection. The decision to treat fat redistribution is frequently determined in the context of associated findings such as insulin resistance and hyperlipidemia, which can result from a combination of anti-retroviral therapy (ART) and visceral fat (VAT) accumulation. Currently, there is no consensus as to whether body fat changes should be treated in the absence of an associated metabolic syndrome. However, metabolic changes and aberrations of fat deposition may independently contribute to increased cardiovascular risk, making treatment of these states an important issue in the long-term management of HIV infection.

There are currently no FDA-approved treatments for central fat accumulation in HIV-infected patients, and efforts to combat HIV- and/or ART-related metabolic derangements and changes in fat distribution have met with mixed results. In part, this is due to an incomplete understanding of the mechanisms underlying these changes.

Metformin, which is used to improve insulin sensitivity in patients with diabetes and polycystic ovarian syndrome, has been shown in HIV infection to improve visceral fat accumulation but exacerbate peripheral lipodystrophy, which may be an independent risk factor for CVD.

Both HIV and ART (specifically PIs and NRTIs) may modulate lipodystrophy via down-regulation of PPAR- $\gamma$ . Thiazolidinediones (TZDs), which also activate PPAR- $\gamma$ , have not been shown to have an effect on VAT in the setting of HIV infection, and have untoward side effects such as weight gain, fluid retention, and lipid abnormalities.

The effects of low-dose growth hormone on VAT are promising, but short-term negative effects on insulin sensitivity were observed, lipodystrophy worsened, its use requires patients to receive regular subcutaneous injections, and the effects appear to diminish quickly. Similarly, GH-Releasing Factor has been shown to decrease visceral fat and improve lipid profile, but has side effects similar to that of growth hormone, requires injection, and its effects also appear to diminish quickly.

Telmisartan is a renin-angiotensin system (RAS) antagonist (via angiotensin receptor type I inhibition) and partial PPAR- $\gamma$  agonist approved for the treatment of essential hypertension. It has also been shown to decrease visceral fat volume, total cholesterol, and LDL levels, and improve fasting glucose levels, HDL, and markers of vascular inflammation in HIV-negative patients with the metabolic syndrome. In subjects with mild to moderate renal insufficiency, telmisartan has been shown to decrease vascular intima-media thickness and improve renal function.

Telmisartan may exert its metabolic effects via multiple pathways.

**Insulin sensitivity:** The PPAR- $\gamma$  and the RAS pathways are believed to affect insulin sensitivity via modulation of adipocyte function and differentiation, and both stimulate adiponectin secretion. Adiponectin decreases circulating lipid levels and improves insulin sensitivity via fatty acid catabolism and inhibition of gluconeogenesis in hepatocytes, and fatty acid oxidation and increased glucose uptake in skeletal muscle tissue. Inhibition of adipocyte maturation via the RAS system promotes the deposition of fat into ectopic sites rather than mature adipocytes, improving insulin sensitivity. Additionally, telmisartan increases insulin-like growth factor I. The improvement in insulin sensitivity seen with telmisartan usage may also be, in part, a secondary effect of fat remodeling (see below), as insulin resistance is known to be associated with visceral adiposity. Lastly, in animal models, an additional adipose tissue-independent mechanism for insulin sensitivity has been suggested for telmisartan.

**Vascular Inflammation:** Telmisartan may decrease vascular inflammation by: improving glucose-induced oxidative stress, PPAR- $\gamma$ -independent TNF- $\alpha$  inhibition, suppression of IL-6, and RAS-mediated nitric oxide synthase modulation.

**Weight loss:** In both humans and animal models, weight loss with telmisartan usage has been observed, an effect postulated to occur via an anorexigenic hypothalamic effect. Decreases in BMI have been shown to correspond with improved serum leptin levels, signifying the loss of adipose tissue.

**Visceral Fat:** Telmisartan may decrease VAT accumulation via multiple mechanisms. First, it has been hypothesized that telmisartan has broad metabolic effects on adipose tissue, including decreased adipocyte size, and may improve caloric metabolism^35. Second, telmisartan directly stimulates adipocyte maturation, including subcutaneous adipocytes, preparing them for lipid uptake. Third, PPAR- $\gamma$  agonism may initiate redistribution of fat from visceral to subcutaneous depots, which is a purported mechanism of the TZD class of agents. Lipid uptake into subcutaneous depots (and movement out of visceral depots) leads to increased energy requirements/metabolism of visceral adipocytes, the end result of which is decreased VAT accumulation. Thus, telmisartan directly acts on adipose tissue and decreases visceral fat accumulation via mechanisms independent of its primary insulin sensitizing effects.

Telmisartan has been studied at standard doses in both hypertensive and normotensive patients, and has been shown to have an excellent safety profile in both populations. It has also been shown to bind PPAR- $\gamma$  differently than the thiazolidinediones, which may explain its improved tolerability.

Telmisartan has not been studied in HIV-positive patients to date, but is an excellent candidate for the treatment of HIV- and ART-related metabolic dysregulation. Its potential effects on visceral fat, lipid levels, and cardiovascular risk are of particular interest, as current therapeutic options remain limited and of unclear benefit. If improvement in these parameters could be demonstrated in HIV-positive patients, telmisartan would be the only agent capable of treating multiple metabolic derangements (hypertension, hyperlipidemia, insulin resistance) in HIV-infected persons, and would decrease: pill burden, risk of drug interactions, adverse events.

The goal of this study is to evaluate the safety and tolerability of telmisartan in virologically-suppressed HIV-positive subjects with central fat gain during effective ART.

### **3.0 STUDY DESIGN**

Single arm, open-label, 24-week study of the addition of telmisartan 40mg po daily to continued ART in subjects with central fat accumulation and suppressed HIV-1 RNA on a stable anti-retroviral regimen.

## **4.0 SELECTION AND ENROLLMENT OF SUBJECTS**

### **4.1 Inclusion Criteria**

- 4.1.1 HIV positive men and women age 18 and older.
- 4.1.2 HIV-1 infection, as documented by any licensed ELISA test kit and confirmed by Western blot at any time prior to study entry or plasma HIV-1 RNA > 2000 on two occasions.
- 4.1.3 Documented central fat accumulation (defined for women/men as: waist circumference > 94/95 cm or a waist-to-hip ratio > 0.88/0.94).
- 4.1.4 HIV-1 RNA documented to be less than 50 copies/mL at screening and undetectable by assay of choice (<50 or <400) for at least 12 weeks prior to entry.
- 4.1.5 Current antiretroviral therapy with a suppressive, highly active anti-retroviral regimen. Subjects must not have changed ART in the 12 weeks prior to entry, and must not be planning to change ART for the 24 week study duration.
- 4.1.6 Systolic blood pressure >115mmHg. Telmisartan has been demonstrated to be safe for use in normotensive subjects.
- 4.1.7 Ability and willingness of subject to provide informed consent.

### **4.2 Exclusion Criteria**

- 4.2.1 Pregnancy (current or within the past 6 months) or nursing.

Note: For females of reproductive potential [defined as women who have had menses in the 12 months prior to entry, or who have not undergone surgical sterilization (hysterectomy, bilateral oophorectomy, and/or tubal ligation)], will need a negative serum or urine pregnancy test in the 48 hours prior to entry. If participating in sexual activity that could lead to pregnancy, study participants must use contraception while on study drug and for 4 weeks after going off study drug.

- 4.2.2 Uncontrolled hypertension. If subjects are currently on a stable anti-hypertensive regimen, they must be willing to add telmisartan to their current regimen and provide documentation from their cardiologist or prescribing physician that the addition of telmisartan is acceptable/not contraindicated. To minimize the potential for aggravation of renal function, if subjects require titration of their antihypertensive regimen while on study, it is asked that ACE inhibitors not be titrated unless other options are not available.

4.2.3 Prohibited concomitant medications: Thiazolidinediones, other members of the angiotensin receptor-blocking class (losartan, irbesartan, olmesartan, valsartan, candesartan), nelfinavir, etravirine. Subjects taking nelfinavir or etravirine will be excluded due to the possibility of increased drug levels via inhibition of cytochrome P-450 2C19.

Note: Subjects requiring amifostine or rituximab must be aware of the increased risk of orthostatic hypotension with the addition of telmisartan. Any subject requiring lithium therapy while on study must have lithium levels monitored closely by their outside physician. All subjects on the above listed medications should provide documentation that this physician is aware of the study protocol.

4.2.4 Subjects with untreated hyperlipidemia must be willing to abstain from initiating therapy for the 24 week duration of the study. Subjects on a stable (>12 weeks) lipid-lowering regimen must be willing to remain on their current dose for the 24 week study duration.

4.2.5 Subjects undergoing treatment for diabetes with oral hypoglycemic agents must be willing to remain on their current dose of insulin-sensitizing agents (metformin/biguanides) for the duration of the study. Titration of other diabetes medications will be permitted.

4.2.6 Screening laboratory values as follows:

- ANC < 750 cells/mm^3
- Hemoglobin <10 gm/dL
- Creatinine clearance <30 ml/min (estimated by Cockcroft-Gault equation using ideal body weight)
- AST or ALT > 3 times ULN

4.2.7 Known, untreated renal artery stenosis.

4.2.8 Unstable coronary artery disease/angina or decompensated congestive heart failure.

4.2.10 Any history of intolerance to any member of the angiotensin receptor blocker class of agents.

4.2.11 Need for ongoing potassium supplementation.

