### Medication History

A medication history must be recorded in the source documents and the CRF. The medication history will include the following:

- Complete HIV treatment history, including start and stop dates of any current or past antiretroviral medication (estimated if the exact dates cannot be obtained), immune-based therapy, or HIV-related vaccines, including blinded study medications.
- Complete treatment history of any prescription medications taken for the treatment or prophylaxis of opportunistic infections, including actual or estimated start and stop dates.
- All prescription medications (in addition to those noted above) taken in the 30 days prior to study entry, including actual or estimated start and stop dates. Only dosages for ART will be required.
- Nonprescription medications taken in the 30 days prior to study entry. Include actual or estimated start and stop dates.
- Alternative therapies and dietary supplements taken in the 30 days prior to study entry. Include actual or estimated start and stop dates.

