## **9.0 SAMPLE SIZE AND ENDPOINTS**

### **9.1 Sample Size**

In a recently reported study of growth hormone releasing factor in HIV lipodystrophy, the FDA determined an 8% change in visceral abdominal fat between the active and placebo arms would define a clinically meaningful difference in VAT volume, assuming a standard deviation of 18.5%. However, we will aim for 10% difference in visceral fat to make it more clinically significant.

Using the parameters recommended by the FDA, we estimate that a sample size of 27 subjects will provide 80% power to detect a 10% reduction in VAT over 24 weeks in subjects treated with telmisartan (two-sided alpha level=0.05). We have increased the sample size to 35 subjects to improve our power to look at secondary endpoints, and to account for potential loss of follow-up. The total sample size is 35 subjects.

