### **9.2 Randomization and Stratification**

Subjects will not require randomization as this pilot study is a single arm, open label trial. Stratification will occur by gender.

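### Co-medication rules and dose recording leave avoidable confounding in a single-arm before-after trial: growth hormone and GH-releasing factor are unrestricted, metformin has no pre-entry stable period, and non-ART doses need not be recorded

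*Protocol*

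**What the plan says.** Protocol 3.0 describes a "Single arm, open-label, 24-week study of the addition of telmisartan 40mg po daily to continued ART". Section 9.2 adds that "Subjects will not require randomization as this pilot study is a single arm, open label trial", and 9.6.1 tests the Week 0 to Week 24 change in VAT with a paired t test.

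On drugs that act on visceral fat, 2.1 says that metformin "has been shown in HIV infection to improve visceral fat accumulation", that low-dose growth hormone looks promising for VAT, and that "GH-Releasing Factor has been shown to decrease visceral fat and improve lipid profile".

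The prohibited list in 4.2.3 opens "Prohibited concomitant medications: Thiazolidinediones, other members of the angiotensin receptor-blocking class" and continues with nelfinavir and etravirine. Section 5.4 only refers back to it. Section 4.2.5 asks diabetics on oral agents to keep their metformin dose, then states: "Titration of other diabetes medications will be permitted". Section 4.2.2 anticipates titration of antihypertensives on study. ART must be unchanged for 12 weeks before entry (4.1.5), and a lipid-lowering regimen must have been stable for more than 12 weeks and then be held (4.2.4).

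The Medication History in 6.5 lists prescription drugs from the 30 days before entry, with start and stop dates, but says of doses: "Only dosages for ART will be required". The Concomitant Medications paragraph puts prescription drugs on the CRF during the study without mentioning dose.

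**The concern.** Without a control arm, limiting and recording other drugs is one of the few protections the estimate has. The protocol uses that protection unevenly. It fixes a pre-entry window for ART and lipid drugs, but not for the agents that its own background section links to visceral fat. A subject who began metformin, growth hormone or GH-releasing factor shortly before the baseline CT, or during the study, would meet every stated rule and stay in the primary analysis. Any resulting fall in VAT would count towards telmisartan.

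For the secondary endpoints, the protocol itself permits drug changes that act on what is measured: diabetes drugs on glucose, insulin and HOMA-IR, and antihypertensives on blood pressure. The direction is not fixed. An increased glucose-lowering drug would look like benefit, while a reduced antihypertensive would hide a fall in blood pressure.

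The protocol also asks for constant doses of lipid-lowering drugs and metformin without requiring the data that would show whether they stayed constant.

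**Working it through.** **Step 1. The plan's own figure.** Section 9.1 gives a 10% reduction, an SD of 18.5%, 80% power and "two-sided alpha level=0.05". The one-sample normal formula gives n = [18.5 × (1.960 + 0.842) / 10]² = 26.86, rounded up to 27. This matches the stated 27; enrolment is 35. The sample size is not affected by this point.

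**Step 2. The rules side by side.**

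| Drug | What the protocol says of it | Stable before entry | Rule on study |
|---|---|---|---|
| ART | background therapy | 12 weeks (4.1.5) | no planned change; dose changes recorded |
| Lipid-lowering drugs | lipids are endpoints | more than 12 weeks (4.2.4) | dose held; dose recording not stated |
| Metformin | improves visceral fat (2.1) | none | dose held in diabetics on oral agents (4.2.5); no rule for new or non-diabetic use |
| Growth hormone | promising for VAT (2.1) | none | none |
| GH-releasing factor | decreases visceral fat (2.1) | none | none |
| Other diabetes drugs | glucose, insulin and HOMA-IR are endpoints (9.4) | none | titration allowed (4.2.5) |
| Antihypertensives | blood pressure is an endpoint (9.4) | described as stable, no period given (4.2.2) | titration anticipated (4.2.2) |

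No other section closes the gap. The drug-based stopping rule in 8.1 points back to 4.2.3, and the as-treated exclusions in 9.6.1 concern the study regimen and missing endpoints.

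**Step 3. What the records can show.** Start dates in the medication history and prescription drugs on the CRF identify a subject who starts a prescribed agent. A dose change in a continuing drug is a different matter. Dose capture is stated for ART and telmisartan, and no such statement is made for the other drugs.

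**Step 4. Illustrative size for VAT.** The documents give neither the number of users nor their effect, so both are assumed. If k of n subjects each have an extra VAT fall of e%, the mean shifts by e × k / n. The figure n = 30 is also an assumption, lying between the protocol's 27 and 35.

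- One user, n = 30: 10/30 = 0.33 to 20/30 = 0.67 points.
- Three users, n = 30: 1.0 to 2.0 points. At n = 35 this is 0.86 to 1.71; at n = 27 it is 1.11 to 2.22.
- Seven users, n = 35: 2.0 to 4.0 points.

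For scale, the standard error at n = 30 is 18.5/√30 = 3.4 points. The smallest significant mean fall is t × 18.5/√n, or 6.4 points at n = 35 and 7.3 at n = 27.

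The chance of a significant fall if telmisartan does nothing (nominally 2.5% in that direction) comes from the noncentral t distribution. The SD is taken as √[18.5² + f(1 − f)e²], with f = k/n:

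| Users | n = 35, e = 10% to 20% | n = 27, e = 10% to 20% |
|---|---|---|
| 1 | 3.1% to 3.7% | 3.1% to 3.9% |
| 3 | 4.5% to 7.4% | 4.8% to 8.2% |
| 7 | 8.8% to 20.6% | 10.1% to 24.4% |

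One user matters little. About one subject in five (7/35) would matter materially. No similar figure can be given for glucose, HOMA-IR or blood pressure, because the documents offer no basis for the frequency or size of titration.

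**The case against.** The strongest reply is that the protocol controls more than a quick reading suggests, and much of it stands.

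- **Metformin.** It is the one diabetes drug that 2.1 credits with improving visceral fat, and it is the one whose dose is held. Permitted titration therefore bears mainly on the glycaemic and blood-pressure endpoints, not on VAT.
- **Removing affected subjects.** A reader might infer from the ART-only dose rule that confounded subjects could never be taken out of the VAT analysis. The documents do not support that. The rule belongs to the pre-entry history, which still asks for start and stop dates, and prescription drugs go on the CRF during the study. Starters can be excluded without knowing doses; only dose changes may be missed.
- **Thiazolidinediones.** A reader might see a contradiction in barring a class that 2.1 says has no shown effect on VAT in HIV. It is not one. Section 2.1 describes shared PPAR-γ activity with telmisartan, a purported redistribution of fat out of visceral depots, and side effects on weight, fluid and lipids. That does not explain why growth hormone and GH-releasing factor have no rule.
- **Attribution.** A reader might infer that these gaps are what prevent attribution to telmisartan. The main cause is the declared design: a single-arm pilot, labelled exploratory in 9.6, with a hypothesis worded as association. Better drug rules would not turn it into a controlled comparison.
- **Frequency.** Nothing in the documents suggests common use of these agents. Section 2.1 notes that both growth-hormone agents need injection and that no approved treatment for central fat accumulation existed.

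What remains is narrower. Eligibility and data capture are set in the protocol, and a later analysis plan cannot recover doses that were not collected.

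**Conclusion.** The point holds as a modest gap in eligibility and recording that is cheap to close. Following the stated rules lets avoidable co-medication effects into an uncontrolled before-after estimate, in addition to the confounding that the design already carries. Compliance with the dose holds in 4.2.4 and 4.2.5 may not be verifiable from the CRF.

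For VAT, the 1 to 2 point shift rests on three assumptions: three users, 30 analysed subjects, and a further fall of 10% to 20% in each user. The true shift may be close to zero. For glucose, insulin, HOMA-IR and blood pressure, the exposure is permitted by the text, but its size and direction are unknown. The calculation of 27 subjects and the enrolment of 35 are untouched.

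**What to change.** 1. **Section 4.2.** Apply the 12-week pre-entry window already used for ART and lipid-lowering drugs to metformin, growth hormone and GH-releasing factor. The 30-day look-back in the medication history would need to match for these agents. Reconcile 2.1 with 4.2.3 and 4.2.5 on their use during the study, including metformin newly started or used outside diabetes. What that rule should be is for the investigators.
2. **Section 6.5.** Replace the ART-only dose rule so that dose and dates of change of glucose-lowering, antihypertensive and lipid-lowering drugs are recorded on the CRF, at entry and on study.
3. **Section 9.6.** Repeat the VAT, glucose, HOMA-IR and blood-pressure analyses without subjects who started or changed a drug relevant to that endpoint. The repeat is supportive, since removing subjects on post-entry events brings its own selection.

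The cost is a few screened subjects lost, a little more data entry and one set of repeat analyses. If the entry window is thought too costly for recruitment, items 2 and 3 are worth making alone.

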## 6.0 CLINICAL EVALUATIONS

### 6.1 Schedule of Events

|                                                                                 | Screen | Baseline* | Week 1 | Week 2 | Week 6 | Week 12* | Week 18 | Week 24* |
|---------------------------------------------------------------------------------|--------|-----------|--------|--------|--------|----------|---------|----------|
| Informed Consent, Patient's Bill of Rights, HIPPA, medical information release  | X      |           |        |        |        |          |         |          |
| Targeted physical exam with weight, blood pressure                              |        | X         | X      | X      | X      | X        | X       | X        |
| Complete physical exam and height                                               | X      |           |        |        |        |          |         |          |
| CT- L4/5                                                                        |        | X         |        |        |        |          |         | X        |
| Mid-waist, hip and neck circumferences and waist/hip ratio                      | X      | X         |        |        |        |          |         | X        |
| HIV-1 RNA                                                                       | X      | X         |        |        |        |          |         | X        |
| Safety labs**                                                                   | X      | X         |        |        | X      | X        | X       | X        |
| CD4 cell counts                                                                 |        | X         |        |        |        |          |         | X        |
| Fasting lipids, hsCRP, banked serum and plasma                                  |        | X         |        |        |        | X        |         | X        |
| Urine samples for markers of oxidant stress and endothelial activation, protein |        | X         |        |        |        | X        |         | X        |

\* Entry, week 12, and week 24 laboratory evaluations are required to be fasting (at least 8 hours).

\*\*Safety labs include: CBC with differential, chemistry panel [including liver enzymes (ALT, AST, Alk Phos) and total bilirubin, serum creatinine], urine or serum pregnancy test. All safety labs, HIV-1 RNA, and CD4 cell counts will be done at local certified laboratories.

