### **Visit 2 Baseline (Week 0, within 30 days of screening)**

Once eligibility has been confirmed, the subject will be scheduled for baseline evaluation, which includes safety lab evaluation and the collection of stored serum, plasma, and urine samples for future analyses. Telmisartan 40 mg po daily will be distributed at this evaluation, and the subject will be counseled (again) regarding adherence and potential medication side effects.

For all subsequent visits, evaluations should be performed +/- 14 days from the expected date. Medication adherence/compliance and method of birth control (if applicable) will be assessed and documented at every visit.

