#### Fasting lipids, Glucose, Insulin, hsCRP

Total cholesterol, HDL cholesterol, LDL cholesterol (direct), triglycerides, hsCRP, and glucose will be performed at entry and weeks 12 and 24 in real time at the local laboratory. Insulin will be batched and analyzed at the end of the study.

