#### Safety Labs

CBC with differential, chemistry panel including liver enzymes (ALT, AST, Alk Phos), total bilirubin, serum creatinine, and urine or serum pregnancy test. All safety labs, HIV-1 RNA, and CD4 cell counts will be done at local certified laboratories.

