### **7.0 TOXICITY MANAGEMENT**

Criteria for subject management and dose interruptions, modifications, or discontinuation will pertain only to toxicities attributable to telmisartan. Toxicities due to drugs in the background regimen should be managed according to standard clinical practice, with the goal of maintaining continuous therapy, if possible.

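### Section 4.2.4 ties eligibility to starting or changing no lipid therapy for 24 weeks, with no severity limit and no stated exception for a Grade 3 or 4 value

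*Protocol*

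**What the plan says.** Section 4.2.4 of the protocol has two parts. For untreated subjects: "Subjects with untreated hyperlipidemia must be willing to abstain from initiating therapy for the 24 week duration of the study". For treated subjects: "Subjects on a stable (>12 weeks) lipid-lowering regimen must be willing to remain on their current dose for the 24 week study duration". Neither part names a lipid level above which it lapses.

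The laboratory exclusions in 4.2.6 cover neutrophils, hemoglobin, creatinine clearance and transaminases, but no lipid.

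In the Schedule of Events (6.1), the row "Fasting lipids, hsCRP, banked serum and plasma" is marked at baseline, Week 12 and Week 24, and not at screening. Section 6.2 fixes the order: "Once eligibility has been confirmed, the subject will be scheduled for baseline evaluation". Telmisartan is handed out at that same baseline visit. Section 6.6 says the lipid tests "will be performed at entry and weeks 12 and 24 in real time at the local laboratory", so the site learns the result during the study.

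Sections 7.2 and 7.3 allow telmisartan to continue through asymptomatic Grade 3 or 4 cholesterol or triglyceride abnormalities, and 8.3 exempts these values from the rule that study drug be withheld.

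**The concern.** The protocol foresees severe lipid values, since 7.2, 7.3 and 8.3 all mention them. Those sections settle only whether telmisartan continues. They do not say whether the subject may be treated for the lipid abnormality and remain on study. The only text on lipid therapy is 4.2.4, and it asks for none to be started or changed.

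Subject safety is what is at stake. A site that takes the 24-week commitment at its word may leave untreated a severe value that it knows about. Another site investigator may treat, without knowing whether the subject can be kept. The adjacent criteria sharpen the contrast: 4.2.2 anticipates titration of antihypertensives and 4.2.5 allows diabetes drugs other than insulin sensitizers to be titrated, while lipids have no counterpart. The primary endpoint is not involved.

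**Working it through.** **Plan's own figure.** The protocol gives no number on this point. Its only calculation is the sample size (9.1), which reproduces: (18.5 × (1.960 + 0.842) / 10)² = 26.86, rounded up to 27. It uses only the VAT change and its SD, so nothing here alters it.

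**Can a severe value enter?**
- Known before entry: yes, if the subject agrees to defer treatment. A subject who will not defer is ineligible, so 4.2.4 screens on willingness and not on severity.
- Not known before entry: yes. Lipids are not measured at screening, and 4.2.6 would not exclude on them.

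**When is it seen again?** Lipids are scheduled at Weeks 0, 12 and 24 only. The safety labs at Weeks 6 and 18 are "CBC with differential, chemistry panel including liver enzymes (ALT, AST, Alk Phos), total bilirubin, serum creatinine, and urine or serum pregnancy test", with no lipids. The next scheduled lipid test after baseline is therefore Week 12, and the period covered by the commitment is 24 weeks.

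**Does another section permit treatment?**
- 4.2.3, 5.4 and 8.1: lipid-lowering drugs are not on the prohibited list, and starting one is not a reason to stop study drug. Nothing forbids treatment on study, but nothing says the 4.2.4 commitment lapses.
- 7.0: its management criteria "will pertain only to toxicities attributable to telmisartan". It adds: "Toxicities due to drugs in the background regimen should be managed according to standard clinical practice". That could reach hyperlipidemia caused by ART, but it does not mention 4.2.4, and a pre-existing elevation due to neither ART nor telmisartan falls outside both clauses.
- 7.2, 7.3, 8.3: these address telmisartan only.
- 8.2: withdrawal by the subject, by the primary care provider, or at the investigator's or IRB's discretion. This ends participation and is not treatment on study.

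**How many subjects? (illustration)** The protocol gives no rate. Assume a Grade 3 or higher proportion p of 2% to 5% among n = 35:
- Expected number = 35p: 0.70 at 2%, 1.75 at 5%.
- P(at least one) = 1 − (1 − p)^35: 1 − 0.98^35 = 0.507; 1 − 0.95^35 = 0.834.

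**What would permitting treatment do to the LDL change? (illustration)** Assumptions, none from the protocol: no telmisartan effect on LDL, SD of the change 20-30 mg/dL, an extra drop d of 30-50 mg/dL in each of k subjects who start therapy, and a paired t test at two-sided 0.05. The number of pairs is taken as 27 to 35, the two counts in 9.1. The mean shift is −d·k/n; for example, one starter gives between −30/35 = −0.9 and −50/27 = −1.9 mg/dL. Rejection rates are simulated.

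| Starters | Mean LDL shift (mg/dL) | False-positive rate |
|---|---|---|
| 1 | −0.9 to −1.9 | about 5% |
| 2 | −1.7 to −3.7 | 5.5-8% |
| 3 | −2.6 to −5.6 | 7-13% |

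This covers LDL only. Triglycerides, Framingham score and metabolic syndrome were not modelled.

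**The case against.** The strongest objection is that 4.2.4 is an entry criterion about willingness and not an on-study ban. The on-study restriction is 5.4, which refers to 4.2.3, and no lipid drug is listed there. Starting one is not a stopping reason, and new prescription drugs are recorded on the CRF. On the text, a subject who starts a statin stays on study and on telmisartan. This stands. A reader might infer that severe hyperlipidemia cannot be treated on study, or that withdrawal is the only way out; the documents do not support either. What remains is that the willingness is expressly for 24 weeks and nothing says when a site may release the subject from it.

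A second objection is oversight. Section 7.2 asks that the study chairs be notified of any Grade 3 or greater toxicity, and 10.4 repeats this where the cause is not clearly documented as unrelated to telmisartan. Section 10.4 also calls for SAE forms for Grade 4 events and real-time notice of serious events to the DSMB, although whether a pre-existing value counts as an event is arguable. Section 9.5 adds monthly team review of Grade 3 or higher labs and quarterly DSMB review of AE summaries. These protections are real and make long neglect less likely. None of them states a treatment rule.

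Third, holding lipid therapy constant is deliberate. Lipids are a secondary objective (1.3.3), and in a single-arm study a new lipid drug confounds the before-after change directly. That justifies the restriction in general, but not the absence of an upper limit.

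Finally, the consent form and the Manual of Operations are not at hand and may contain guidance. An exception to an eligibility commitment in the protocol should still stand in the protocol.

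**Conclusion.** The point holds as a cheap improvement to subject safety. Section 4.2.4 asks for a 24-week commitment without a severity limit, 4.2.6 and the visit schedule let a severe value through, and 7.2, 7.3 and 8.3 do not say what may be done about it. A site that applies 4.2.4 literally could leave a known Grade 3 or 4 cholesterol or triglyceride value untreated for up to 24 weeks. A site that reads 4.2.3, 5.4 and 8.1 instead could treat and keep the subject.

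The number of subjects affected cannot be known from the protocol. The 51-83% chance of at least one rests wholly on the assumed 2-5% rate, and the DAIDS grading table that defines Grade 3 is cited but not reproduced. The LDL figures rest on assumed inputs too. They illustrate the cost of the fix and do not measure the harm of leaving the text alone. The VAT endpoint and the sample size are unaffected.

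**What to change.** Add to 4.2.4: *Lipid-lowering therapy may be started or changed for a confirmed Grade 3 or higher lipid elevation found at baseline or on study; the subject remains on study and the drug, date and dose are recorded on the CRF.* Cross-refer to this sentence from 7.2 and 7.3. Below Grade 3, leave 4.2.4 as it is. Naming on-study elevations as well as baseline ones means a single rule also covers a value first seen at Week 12. Identify the treated subjects when the Week 0-24 changes in lipids, Framingham score and metabolic syndrome are reported.

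Cost: one sentence, two cross-references, and one unscheduled repeat fasting lipid test per affected subject to confirm the value. Prescription drugs already go on the CRF (6.5), so the recording burden is small. The downside is that a few treated subjects may confound these secondary endpoints; section 9.6 describes the analyses as exploratory.
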